**Fig. 1 Fig1:**
[figure not shown]
Study flow chart. T2DM, type 2 diabetes mellitus; BMI, body mass index; PA, physical activity

### Eligibility criteria

This study aims at tertiary prevention and therefore patients have to be diagnosed with a manifest non-insulin-dependent diabetes mellitus (doctor diagnosed) to be eligible to participate. They further have to be overweight (BMI ≥25 kg/m^2^), between 45 and 70 years of age, have used a smartphone regularly during the last year before the study and give their written informed consent. Because questionnaires will be filled out as part of this study, sufficient proficiency of German is required. Patients will be excluded if any one of the following criteria is applicable:▪ Impaired physical mobility (participants have to at least be able to walk short distances indoors without a walking aid and without help of another person).▪ Regular PA before the study (≥150 min moderate intensity daily PA per week or >1 endurance or strength training session per week of more than 30 min in duration).▪ Other clinically significant concomitant disease states (e.g., renal failure, hepatic dysfunction, cardiovascular disease, etc.).▪ Inability to follow the procedures of the study, e.g., due to language problems, psychological disorders, dementia, etc., of the participant.▪ Resting systolic blood pressure >170 mmHg, resting diastolic blood pressure >100 mmHg.▪ Participation in other clinical studies in the last 4 weeks.

### Experimental and control intervention

#### Overview

The duration of the intervention is 24 weeks. In the experimental group the intervention consists of:Individualized multidimensional (strength, endurance, balance, flexibility) home-based exercise and daily PA promotion administered through the use of MOBIGAME following established PA guidelines [47].Consultations provided by a sports medical expert via telephone, including personal attention and instruction as well as technical support

In the control group the intervention consists of:One-time lifestyle counseling (standard of care) including the promotion of baseline activities of daily life [57] as well as a structured exercise plan including strength and endurance exercises with moderately increasing intensity and duration, essentially comparable to the content of MOBIGAME, which is to be implemented autonomously.Consultations provided by a sports medical expert via telephone, including personal attention and instruction.

#### Common aspects for both groups

In both groups a sports medical expert will provide a given number of personal exercise consultations on the telephone (weeks 1 and 2) as well as a face-to-face consultation at week 0, thus guaranteeing that the control group receives the same number of consultations as the experimental intervention group. For an overview of the study schedule, see the Standard Protocol Items: Recommendations for Interventional Trials (SPIRIT) schedule [58] (Fig. 2).

**Fig. 2 Fig2:**
[figure not shown]
Schedule of enrollment, interventions and assessments according to the Standard Protocol Items: Recommendations for Interventional Trials (SPIRIT). 6MWT, 6-Minute Walk Test; ECG, electrocardiogram; HRQOL, health-related quality of life; STS, Sit-to-Stand Test

#### Experimental intervention details

The experimental intervention aims at improving participants’ motivation to exercise in the short and especially in the mid to long run through the use of MOBIGAME and thereby increasing daily PA. MOBIGAME features numerous different exercises (see Table 1) and exercise regimens including strength and endurance workouts as well as balance and flexibility exercises (a total of over 130 exercises) that concur with generally accepted PA guidelines [46, 47]. The strength exercises span over a wide range of different difficulty and intensity levels. Each exercise contains up to 15 variants with up to 30 different levels regarding repetitions, bouts and duration for each variant. All exercises are designed in a way that makes it possible for players with any fitness level to gradually progress with their workout routine while increasing workout intensities at an individualized pace.

**Table 1 Tab1:** Overview of exercises included in MOBIGAME

Category	No.	Exercise (no. of variants)
Strength	1	Hip/knee extension, dynamic (15)
	2	Knee extension, static (3)
	3	Leg lift, frontal/lateral (9)
	4	Arm elevation (7)
	5	Arm abduction (7)
	6	Elbow extension/shoulder protraction (6)
	7	Back extension, dynamic (6)
	8	Upper back/shoulder extension, static (4)
	9	Abdominals, static (5)
	10	Abdominals, dynamic (10)
Endurance		**Aerobics**
	1	March (2)
	2	Tap (6)
	3	Step touch (4)
	4	Out-In (2)
	5	V-step (2)
	6	Box-step (2)
	7	Grapevine (2)
	8	Leg curl (2)
	9	Knee lift (2)
	10	Front kick (2)
	11	Heel dig (2)
		**Walking**
	1	Continuous (1)
	2	Interval (4)
Flexibility	1	Chest/upper back (2)
	2	Torso (1)
	3	Neck (2)
	4	Lateral torso (1)
	5	Ischiocrural muscles (2)
Balance	1	Two-leg stand (5)
	2	Tandem stand (5)
	3	One-leg stand (5)

Data captured in bold indicates that all Aerobics exercises as well as the two Walking exercises are sub-categories of the Endurance exercises

Endurance workouts include a wide variety of walking exercises with different walking speeds and exercise modalities as well as aerobic workouts (Table 1). Walking exercises are to be conducted outdoors and include continuous trainings as well as interval trainings. Since the 6MWT speed is used as a reference, the proposed walking speeds during the workouts are individually adjustable (e.g., 70% of 6MWT speed). To prevent players from being inattentive to their surroundings because of smartphone distraction, walking exercises are not visualized on the smartphone’s screen. Instead, players are advised to keep the phone in their pocket throughout the exercise, which in addition will guarantee a more accurate tracking of the players’ step count during the exercise. Before the start of each walking exercise, along with the exercise instruction, the players are further advised to ensure a safe environment that is suitable for the upcoming walking exercise. This precaution in design is based on prior research on location-based games that involve explorative, walking activities in public space; it had been shown that there was a need to focus the player’s attention away from the gaming device’s screen during such gameplay situations to avoid dangerous encounters [59]. Aerobics moves can be executed with or without arm movement, indoors as well as outdoors. The combination of indoor and outdoor exercises in an exergame application is a novelty and offers a vast variety of different endurance workout opportunities to meet individual exercise preferences. Instructional videos are available for all exercises (strength, aerobics, balance and flexibility) to ensure correct and safe execution. The algorithms for the individualized exercise training are based on the ACSM and EACPR principles of exercise training [46, 47] and several exercise intervention studies in normal and overweight subjects and patients [60–63]. The training progression in the game is monitored through the repetition of the baseline tests and subsequent adaptions in the exercise/intensity selection. Specific test scores are linked to specific exercises and difficulty levels, so that for example players with higher scores in the STS will get a higher (entry) difficulty level for a specific leg strength exercise than players with a lower score. In addition to these adaptions, the user has the option to rate the intensity of each exercise upon its completion, directly affecting the intensity of the next workout. The rating scale used is a simplified version of the 15-point Borg Scale [64]. In simple terms, a rating of “too hard” will result in a lower difficulty/intensity level in the next workout; a rating of “too easy” will result in a higher difficulty/intensity level in the next workout. Five consecutive ratings of “just right” of the same exercise will result in the suggestion of a higher intensity level in the next workout. The combination of objective as well as subjective measures to control the training progression was chosen to enable unbiased feedback to the player through the repetition of the baseline tests while keeping the player in control of the game at all times, thereby facilitating the long-lasting enjoyment and high levels of self-efficacy that are known to positively influence exercise adherence [49].

A key element of the story line of MOBIGAME is the restoration of a garden. The garden used to be a beautiful place until the Schweinehund came and destroyed it, causing all of the animals that used to live in the garden and help maintain it to leave. In German, “innerer Schweinehund” (inner swine hound) is used as a self-depreciating idiom denoting a form of lazy procrastination, usually of the physical kind, that needs to be overcome to get yourself going. The player’s task is now to help restore the garden by planting trees and flowers and thereby attracting the animals to come back into the garden while at the same time taming the Schweinehund. The garden as the main setting was purposefully chosen as gardens and the activity of gardening have been shown to be highly appealing to the target group [65] and to be effective in reducing stress and stress related-illness such as cardiovascular diseases, depression, reduced immune function and chronic fatigue [66]. In this regard, it has been shown that simply viewing a green space through a window can relax people and reduce stress levels [66, 67]. In our approach, the viewing of this green space (i.e., the garden) occurs through the smartphone screen. Particularly the engagement in gardening activities is very effective in alleviating stress and has been shown to significantly decrease cortisol levels [68]. Research has further shown that nurturing plants from seed to maturity evokes feelings of curiosity, competence and enjoyment, all of which contribute to successful stress management [69, 70]. While we are aware that artificial gardening on a smartphone screen is not identical to an actual gardening experience, the positive and de-stressing character of this activity may still partially be transmitted to the player The animals are humanized (walk upright, wear clothes), always friendly and very likable and represent typical human character traits. Some have even acquired typical human vices such as laziness, sulkiness, contempt or moodiness that the player can help them break by playing the game regularly and thus being regularly physically active. Every activity (in-app workouts as well as steps walked during the day) is rewarded with water or building materials needed to restore the garden. When designing the game, close attention was paid to defined principles and mechanisms such as the inclusion of rules, clear but challenging goals, fantasy, progressive levels of difficulty, interactivity, player control, uncertainty, feedback and a social element [71, 72]. The game mechanics are further anchored in the 40-item CALO-RE taxonomy of behavior change techniques [73]. In this regard particularly “goal setting,” “action planning” and “providing rewards contingent on successful behavior” (i.e., the player sets the goal to complete a super-challenge that requires regular activity on several consecutive days in order to receive a special reward), as well as “providing feedback on performance” (i.e., all of the player’s activity and achieved goals are recorded and summarized in a general overview), are implemented in the game mechanics to help players integrate more PA into their daily routines. “Environmental restructuring” is used quite visibly in the main story line (restoring of the garden) while at the same time and more subtly leading to the development of exercise habits and routines (“prompting practice”) that are supported by the “use of follow-up prompts” (i.e., reminder notifications). The players are encouraged to seek support from the humanized animals to achieve their goals (“elicit social support”) and to keep the Schweinehund away, as failing in doing so will interfere with a successful garden restoration (“fear arousal”). As its ability to provide (lasting) enjoyment is critical to the success of any game, the focus was laid most importantly on this specific factor [74]. While it has been pointed out that for serious games the fun may only need to exceed its traditional analog (health class, lectures from care providers, etc.) to be considered successful [75], we aimed to create an appealing exergame that players want to play because it gives them pleasure by featuring just the right balance between fun and seriousness [51, 76]. Figures 3, 4, 5, 6, 7, 8 and 9 show screenshots of MOBIGAME to illustrate how the gameplay and exercises work from the user perspective.

**Fig. 3 Fig3:**
[figure not shown]
Illustration of the gaming concept of MOBIGAME

**Fig. 4 Fig4:**
[figure not shown]
Illustration of the undeveloped garden before starting the exercise (**a**) and the fully developed garden as a result of regular exercise (**b**)

**Fig. 5 Fig5:**
[figure not shown]
Screenshot of the exercise mode: (**a**) Step-by-step instructions, including a video of an animated stick figure, are available for all exercises to ensure correct execution. (**b**) Tracking of exercise execution via camera, audio sensor or motion sensor tracking

**Fig. 6 Fig6:**
[figure not shown]
Screenshot of the exercise mode: Training focus (**a**), type of in-app reward (**b**) and required materials (**c**) are clearly stated before the start of the training

**Fig. 7 Fig7:**
[figure not shown]
Screenshot: Overview of completed exercises by muscle group (**a**) or by type of exercise (**b**)

**Fig. 8 Fig8:**
[figure not shown]
Screenshot of activity overview: (**a**) Average steps and average minutes of activity per week, month (displayed) or year. (**b**) Day view of steps walked, daily step goal and information if step goal was reached

**Fig. 9 Fig9:**
[figure not shown]
Screenshot of training overview: Total number of completed strength exercises. Exercises displayed are lunge (“Ausfallschritt”), leg lift (“Beinheben”), squat (”Kniebeuge”) and push-up (“Liegestütze”)

At the end of the baseline examination, MOBIGAME is installed on the participants’ smartphones (Fig. 2). The participants only receive very basic instructions on how to use and control the app since MOBIGAME was designed to be self-explanatory including a built-in tutorial that explains all of the game’s features to the player at the appropriate time. Participants further do not receive any instructions on how often to use the app because this study seeks to evaluate the motivating character of MOBIGAME by itself and thereby its suitability to increase regular PA.

#### Control intervention details

The control intervention focuses on promoting daily PA through a one-time lifestyle counseling, which will be administered by a sports medical expert. All participants in the control group receive a booklet containing information on the benefits of regular PA for health, opportunities to integrate more PA into the daily routine and illustrations of recommended exercises and activities (comparable to the exercises included in MOBIGAME) as well as 24 weekly exercise logs [77] to check off completed workouts and record additional activities. Increases in daily PA in the control group are possible but are not expected to be of the same extent or persistence as in the experimental group because a daily reminder and the motivating character of a game are missing.

### Study data

#### Characterization of participants

Baseline data of participants are assessed during the recruitment process and within the baseline assessment (see Fig. 2). Demographic data (sex, age, socioeconomic status, smoking status), anthropometric data (weight, height, waist and hip circumference, body composition) and resting blood pressure are assessed by a sports medical expert. Medical history (including drug history and concomitant medication) as well as allergies are assessed during a general physical examination by a physician. PA is assessed using the Freiburg Questionnaire of physical activity [78] as part of the screening during recruitment.

#### Primary outcome

The primary outcome is daily PA measured as steps per day after 24 weeks. It is assessed in a 1-week tracking period during the week before the start of the intervention as well as during the first week after the 24-week intervention using a VivoFit 2 pedometer wristband (Garmin International Inc., Olathe, KS, USA). The displays of the wristbands in both groups will be irreversibly blackened out so that the daily activity can only be viewed by the study personnel via the wristband’s software and a motivating character of PA feedback by the device can be ruled out.

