### Timeline

The duration of the entire MOBIGAME project is 50 months (January 2014 to February 2018). Development of MOBIGAME was completed in February 2016. Recruitment of participants started in January 2016 and is expected to end in June 2017 (18 months). Examinations started in August 2016. The last participant is expected to finish the intervention in December 2017. Altogether, the period between “first patient in” and “last patient out” is 20 months.

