### Sample size

Determination of sample size was based on the primary outcome. On the basis of a previous study [43] and our own experience, we assumed that the expected difference in daily PA after 24 weeks between participants in the experimental intervention and those in the control group would be 2500 steps per day. We further assumed that the standard deviation given either study group would be 3000 steps per day [43]. By including daily PA (steps per day) at baseline as a covariate in the analysis, we aim to further reduce error variability and therefore assumed that the correlation between baseline and outcome daily PA will be 0.7. With a significance level of 0.05 (2-sided), the sample size needed to attain a targeted power of 90% for showing superiority of the experimental intervention over control was determined as a total of 34 participants (17 in each group). While we aim to achieve complete capture of all data from all participants, it is unavoidable that some participants will fail to provide outcome data. We will therefore increase the proposed sample size by 20%, so that we will include a total of 42 participants (21 in each group).

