### Statistical methods

The statistical analysis will conform to the pre-specified statistical analysis plan described below. Following the intention-to-treat analysis strategy, participants will be analyzed in the groups exactly as randomized.

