#### Main analyses

The main analyses will be performed on the assumption that missing outcome data are missing at random and therefore will be based on complete cases only.

The primary outcome of daily PA (steps per day) after the 24-week intervention and further outcomes will be analyzed by analysis of covariance (ANCOVA) [83]. The results will be presented as differences in outcome (with 95% confidence intervals) between participants in the experimental intervention and those in the control group, adjusted for the corresponding values at baseline. In the case of chance imbalances at baseline, this will remove a possible bias in the estimate of the effect of experimental intervention over control, while, at the same time, yielding a more precise estimate and accordingly more powerful test for the difference between groups.

Normality will be assessed using normal quantile-quantile plots of the residuals, and to assess variance homogeneity, we will use Tukey-Anscombe plots. If the residual plots indicate departure from model assumptions, suitable transformations of the outcome will be considered [84].

For the secondary outcome, each group will be analyzed descriptively with respect to program adherence.

Finally, correlations between MOBIGAME adherence and acceptance of MOBIGAME (TAM questionnaire score, see Additional file 2) will be analyzed using Spearman’s rank correlation coefficient.

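### The two step-count weeks lie about half a year apart, so baseline-only ANCOVA leaves any annual cycle in the residual, enlarged; two calendar-date terms would avoid a needlessly wide confidence interval

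*Protocol article*

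**What the plan says.** - **Timing of measurement** (Primary outcome): steps per day are recorded by wristband in a "1-week tracking period during the week before the start of the intervention as well as during the first week after the 24-week intervention".
- **Calendar** (Timeline): "Examinations started in August 2016. The last participant is expected to finish the intervention in December 2017". Recruitment is expected to close in June 2017, so baseline weeks fall between about August 2016 and June 2017.
- **Primary model** (Main analyses): ANCOVA, with the group difference "adjusted for the corresponding values at baseline". No date or season term is named.
- **Status of that model** (Statistical methods): "The statistical analysis will conform to the pre-specified statistical analysis plan described below". The primary model is therefore fixed in the article and not deferred to a separate document.
- **What the baseline covariate is expected to do** (Sample size): the plan assumes that "the standard deviation given either study group would be 3000 steps per day", and it "therefore assumed that the correlation between baseline and outcome daily PA will be 0.7", in order to reduce error variability.
- **Allocation** (Allocation and blinding): permuted blocks of randomly varying size. No stratification by season is mentioned.

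**The concern.** Baseline adjustment helps when whatever makes a person high at baseline also makes that person high at the end. An annual cycle measured half a year apart does the reverse. Someone who starts near the seasonal peak is measured near the trough at the end, and the other way round. The slope on baseline is positive because stable differences between people dominate, so the seasonal part of the baseline is carried into the adjusted outcome with the wrong sign and adds to the outcome's own seasonal part.

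Because entry is spread over most of a year, season differs between participants and is not absorbed by the intercept. At stake is precision of the primary comparison in a trial of 34 to 42 people. The calendar date that would remove this noise must be known in order to schedule the tracking weeks.

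**Working it through.** **1. The plan's own figure.** Inputs from Sample size: difference 2500, SD 3000, correlation 0.7, two-sided 0.05, power 90%.
- Residual SD = 3000 × √(1 − 0.7²) = 2142.
- With 17 per group, SE = 2142 × √(2/17) = 735. Noncentral t power (31 df) is 0.909; with 16 per group it is 0.891. The stated 17 per group reproduces.
- 17 × 1.2 = 20.4, rounded up to 21 per group, 42 in total.

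**2. Phase.** The mid-points are 25 weeks apart: 25/52 × 360° = 173°, cosine −0.993. For an annual cosine, the seasonal part of the outcome is almost exactly the negative of the seasonal part of the baseline.

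**3. Effect on the residual.** Let A be the amplitude (peak minus yearly mean, steps/day). It is an assumption; the documents give none. Add the cycle on top of the planning values, with dates spread evenly over the year:
- Variance V = 3000² + A²/2
- Covariance C = 0.7 × 3000² − 0.993 × A²/2
- Slope b = C/V; residual variance = V − C²/V
- Seasonal swing left after adjustment ≈ (1 + b) × A

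Worked for A = 1000: V = 9.50 million, C = 5.80 million, correlation 0.61, residual SD 2440. For A = 500: V = 9.125 million, C = 6.18 million, correlation 0.68, residual SD 2224. With date terms the residual SD returns to 2142 in both cases.

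At 17 per group these residual SDs give power 0.888 (A = 500) and 0.825 (A = 1000), against 0.908 with two date terms. This formula treats season as if it fell at random across the arms, so it overstates the loss under blocked allocation.

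**4. Simulation of the design.** Assumptions: 34 participants, starts spread evenly from August to June, random permuted blocks of 2, 4 or 6 (the protocol does not disclose its block sizes), mid-July peak, true difference 2500, 6000 runs per setting. Each cell gives baseline-only, then with sine and cosine terms.

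| A | True SD of estimate | Mean model SE | Power | Type I error |
|---|---|---|---|---|
| 0 | 749 / 753 | 739 / 742 | 0.910 / 0.904 | 0.042 / 0.044 |
| 500 | 765 / 762 | 767 / 745 | 0.885 / 0.895 | 0.048 / 0.052 |
| 1000 | 760 / 743 | 837 / 746 | 0.846 / 0.898 | 0.029 / 0.046 |

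The mean estimate is about 2500 in every cell, so there is no bias. The true spread of the estimate hardly moves, because blocking already balances season between arms. The model-based SE does grow, because the residual counts all the seasonal noise. The interval is therefore too wide and the test conservative.

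Mean interval widths from a separate simulation of the same design:
- A = 500: 3126 against 3046 (3126/3046 = 1.026).
- A = 1000: 3414 against 3047 (3414/3047 = 1.120).
- A = 300: about 0.6% wider.
- A = 0, from the table: 2 × 2.040 × 739 = 3015 baseline-only and 2 × 2.045 × 742 = 3035 with two terms, a cost of 0.7%.

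**5. If the planning values already include season.** Take total SD 3000 and total correlation 0.7, and remove the cycle. For A = 500, the within-season variance is 8.875 million and the covariance 6.42 million; residual SD is 2055, and power with date terms 0.929. For A = 1000 it is 0.980. Baseline-only power stays at the planned 0.909.

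**6. One term or two.** A single day-length term peaks in June. If steps in fact peak in late August, at A = 500 the mean width is about 3140 with or without it. A sine and cosine pair fits any phase. With a fixed gap between the weeks, the baseline date also sets the outcome date, so one pair is enough.

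**The case against.** The strongest case against is that baseline-adjusted ANCOVA is a standard, valid primary analysis and nothing in the article is misstated. Leaving out an optional covariate in a small trial is a legitimate preference. The size depends entirely on an amplitude that the documents do not give, and near 300 steps/day or below the effect is negligible. The support within the article is thin: "Walking exercises are to be conducted outdoors and include continuous trainings as well as interval trainings" describes the app arm only, and the same section lets aerobics be done indoors. All of this stands, and it limits the point to an inexpensive improvement.

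It is also fair that the Sample size section does not call its SD and correlation within-season values. Read plainly, 0.7 is the correlation expected at this trial's own spacing, and then planned power is intact.

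A reader might infer more than the text supports:
- *That season biases the comparison.* Both arms are randomized in blocks over the same calendar period, and the simulated estimate is unbiased.
- *That the SE of the difference truly rises in step with the residual SD.* Only the reported SE does; the actual spread changes by about 2% at A = 1000 (760 against 743).
- *That baseline adjustment is harmful overall.* At A = 500 it still brings the SD from about 3021 (√9.125 million) down to 2224.
- *That every participant is measured at opposite extremes.* With a July peak, people starting around October or April sit near the yearly mean both times.

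The objection does not remove the mechanism: for the seasonal part alone, the baseline covariate works against its stated purpose. The remedy costs little on either reading of the planning values.

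**Conclusion.** The point holds as a minor one about precision. The schedule puts the two step-count weeks in near-opposite phase of the year, and the baseline-only model leaves any annual cycle in the residual, enlarged by a factor of about 1 + b (roughly 1.7 at the planned correlation). The consequence is a wider, conservative interval, with valid inference and a stated sample size that is correct on its own inputs.

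The size is conditional on the assumed amplitude and on season coming on top of SD 3000 and correlation 0.7. Interval width is then about 0.6%, 2.6% and 12% greater at 300, 500 and 1000 steps/day. The power loss is about 0, 0.5 to 1 and 5 to 7 percentage points, varying with the phase of the cycle and between simulations. If the planning values already contain season, there is no shortfall and the date terms are pure gain.

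**What to change.** In Main analyses, add to the primary ANCOVA, alongside baseline steps, the sine and cosine of the tracking-week date on an annual cycle. Report the baseline-only model as a sensitivity analysis. Prefer the pair to a single day-length term, whose benefit depends on guessing when steps peak. Fix the terms before outcome data are compared by group, since a later addition would look data-driven.

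The cost is one sentence and two degrees of freedom, under 1% of interval width if steps do not vary by season. No new measurement is needed: the article does not say that the dates are stored, but they follow from the visit schedule. Sample size, allocation and conduct are unchanged.
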